### Data management and analyses

In this study, we believe a data monitoring committee is not needed as we are not testing a medicinal product or invasive product or device. We will use an established data management team to control data management and quality. In addition, we will not conduct interim analyses to make decisions on whether to stop the trial.

Data will be collected using electronic data capturing (EDC). We will use tablets in which a simple case report form (CRF) is pre-programmed. Data will be entered in RedCap (Research Electronic Data Capture). REDCap is a secure, web-based application designed to support data capture for research studies, providing 1) an intuitive interface for validated data entry; 2) audit trails for tracking data manipulation and export procedures; 3) automated export procedures for seamless data downloads to common statistical packages; and 4) procedures for importing data from external sources [52]. RedCap will only be accessible by authorized users. The data of participants is coded and will be treated anonymously. Data validation will be conducted using the automated query feature. Statistical tests will be performed at a two-sided significance level of 0.05. Analyses will be performed with Statistical Product and Service Solutions (IBM SPSS Statistics, Chicago, USA).

#### Baseline characteristics

Baseline characteristics data will be summarized for all participants and for the two arms. The characteristics information includes patient identification number, place of living/work, contact phone number, sex, age, referral option, phone number of treatment supporter, name of health facility, DOT option (health facility DOT or home-based DOT), and HIV status, including co-medication. We shall also take sputum smear and isoniazid urine tests for measuring treatment outcomes.

#### Primary objective

To answer the primary objective, we will compare adherence measures between the different arms. We will compare the mean adherence levels (percentage of medication taken) between arms and we will also compare percentage of participants that adhered according to the cut-off levels of 99%, 95%, 90%, and 75% (for example, 10% of patients had a mean adherence level of 99% or more). For continuous adherence levels, we will use *t*-tests or nonparametric tests depending on distribution of data. For cut-off levels, we will use χ^2^ tests. To account for the cluster effect in the analysis, we will conduct mixed effects regression models.

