**Discussion:**

If the intervention shows a significant effect on adherence and the devices are accepted, accurate, and sustainable, the intervention can be scaled up within the National Tuberculosis Programmes.

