### Measurements

#### Main objective

To answer the main objective on effectiveness of evriMED on treatment adherence and outcome, we will measure adherence to treatment in several ways and treatment outcome through sputum smear conversion and relief of symptoms. Adherence will be measured through pharmacy refill counts. This means that, at each visit, we will count the number of leftover medication that the participant brought. As such, they will be instructed to bring their leftover medication always. Furthermore, we will use self-report by asking how many pills were missed since the last visit. Furthermore, we will have adherence data from the evriMED boxes for those participants who are in the treatment arm. These data will show when the pillbox was opened, which is a proxy for medication intake. Based on that, we can count the number of days the box was opened. Adherence will be calculated by ‘Number of days when pills were taken’ divided by ‘Number of days that pills had to be taken’. Sputum smear conversion will be used as treatment outcome and measured according to standard care at month 2, month 5, and month 6 of the treatment course.

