### Sample size calculation and randomization

We calculated that to be able to detect a difference of mean adherence from 79% to 90%, with a power of 80% and significance of 0.05, we would need a sample size of 336 (168 in each arm). As we will use cluster randomization, we used a cluster correlation factor of 0.01. We will need to include 600 patients, 50 in 12 clusters. Considering a drop-out rate of 10%, we anticipate enrolling 660 participants in total. For a period of 8 months, all patients diagnosed with susceptible TB will be asked to participate in our study.

The whole Kilimanjaro Region was divided into 12 clusters based on location in the district, level of health care facility, and number of TB cases in 2017 in each clinic. These clusters were then randomly assigned to provide either standard of care or standard of care and pillbox. A random variable was generated in a dataset containing the clusters. Then, the clusters were sorted using a random variable. The first six clusters were assigned to intervention and the last six to control. Randomization was done using Stata 15.1.

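### The primary objective is answered by at least ten unranked between-arm adherence tests, each at 0.05, and neither the analysis section nor the sample size says which one decides

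*Protocol article*

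**What the plan says.** - **Measures.** Under Measurements, Main objective, the article says "we will measure adherence to treatment in several ways and treatment outcome through sputum smear conversion and relief of symptoms". Refill counts and self-reported missed pills are collected in both arms. The evriMED opening data exist only in the intervention arm, so they cannot be compared between arms.
- **Forms.** Under Data management and analyses, Primary objective, the adherence measures are compared between arms as means, and then "we will also compare percentage of participants that adhered according to the cut-off levels of 99%, 95%, 90%, and 75" per cent. The tests listed are t-tests or nonparametric tests for the mean and chi-squared tests for the cut-offs, with mixed effects models to allow for clustering.
- **Level.** "Statistical tests will be performed at a two-sided significance level of 0.05". No order of testing and no adjustment is given.
- **Sample size.** The trial is sized to "detect a difference of mean adherence from 79% to 90%, with a power of 80% and significance of 0.05", which gives 168 per arm before clustering. The section does not say by which measure adherence is taken.
- **Decision.** The Discussion part of the Abstract makes scale-up possible "If the intervention shows a significant effect on adherence and the devices are accepted, accurate, and sustainable". It does not say on which measure or in which form the effect must appear.

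**The concern.** A primary objective needs one comparison that decides it, or a rule for combining several. Here the plan offers two measures, each in five forms, and gives them equal standing. A team following the text could report whichever of the ten reached 0.05 and say truthfully that it was a planned primary analysis. The two measures may disagree, and so may the cut-offs. The Limitations section itself says that self-report and refill counts overstate adherence. At stake is a recommendation to a national programme that could rest on the most favourable of ten comparisons.

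**Working it through.** **1. Which endpoint does the sample size support?** Inputs, from Sample size calculation and randomization: 79% versus 90%, two-sided 0.05, power 80%.

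Two proportions, pooled variance under the null, mean proportion 0.845:

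n = [1.960 × √(2 × 0.845 × 0.155) + 0.842 × √(0.79 × 0.21 + 0.90 × 0.10)]² / 0.11² = 168.7 per arm.

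This reproduces the stated 168 (336 in total), apart from rounding.

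Two means, n = 2 × (1.960 + 0.842)² × SD² / 11². Setting n = 168 gives SD = 11 × √(168 / 15.70) ≈ 36 percentage points. No SD is stated. Adherence lies between 0 and 100%, so with means of 79% and 90% the largest possible average variance is (0.79 × 0.21 + 0.90 × 0.10) / 2 = 0.128, an SD of about 35.8 points. That limit is reached only if every patient takes all pills or none. The figure therefore does not come from a realistic comparison of means.

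The Background gives the source of the 79%: the share of Kilimanjaro patients who reached 95% adherence. The wording points to the mean; the number and the formula point to the 95% cut-off.

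**2. Count of tests.** Two measures in both arms × (1 mean + 4 cut-offs) = 10.

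**3. Chance of at least one false-positive result.** The correlations between the tests are not in the documents, so they are assumed and varied. Each test is taken to hold its own 5% level, which presumes proper allowance for clustering.

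- Independent tests (upper reference): 1 − 0.95¹⁰ = 0.40.
- Common correlation ρ between all ten tests: 1 − E[{Φ((1.96 − √ρ·X)/√(1−ρ)) − Φ((−1.96 − √ρ·X)/√(1−ρ))}¹⁰], with X standard normal. For results in favour only, the second Φ is dropped.

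| ρ | Either direction | In favour of evriMED |
|---|---|---|
| 0.3 | 0.35 | 0.18 |
| 0.5 | 0.29 | 0.14 |
| 0.6 | 0.25 | 0.13 |
| 0.7 | 0.21 | 0.11 |
| 0.9 | 0.13 | 0.06 |
| One test | 0.05 | 0.025 |

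- Structured model: adherence follows a beta distribution (three shapes, means 0.79 to 0.91), the two measures are correlated 0.3 to 0.9, and the correlations among mean and cut-offs follow from the distribution. The ten tests give 0.25 to 0.32 in either direction and 0.13 to 0.16 in favour. One measure with its five tests gives 0.17 to 0.18.
- Clustered simulation: 12 clusters of 50, intracluster correlation 0.01, 79% of patients at or above 95% adherence, cluster-level t-tests on 10 degrees of freedom, measures correlated 0.3 to 0.6. The ten tests give 0.26 to 0.28; five tests on one measure give about 0.15.

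**The case against.** The best defence is that the mean is meant to be primary. The sample size is worded on mean adherence, and the Primary objective section puts the mean first and brings in the cut-offs as an addition. That is a natural reading, but it fails on two counts. It leaves open whether the mean is by refill count or self-report, and the calculation it relies on is one for proportions built on a 95% cut-off.

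A second defence is that an analysis plan may name the endpoint. It may, and detail left to such a plan would be no finding. But the protocol does not leave the matter open: it states what answers the primary objective, and states it as an unranked set.

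Two objections stand. The size of the inflation depends on correlations that the documents do not give, so no single multiple of 5% can be stated as a result. And the two-sided figure counts results against evriMED as well; for a false claim of benefit the relevant figure is about half, compared with 2.5%.

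A reader might also infer that sputum conversion and symptom relief are further routes to success, because the Main objective includes them. The documents do not support that: the Primary objective section gives no test for them, and the Conclusions make improved treatment outcomes an added condition. Nor does the sample size statement, "Considering a drop-out rate of 10%, we anticipate enrolling 660 participants in total", show that patients who drop out leave the analysis. It only inflates enrolment, and how drop-outs are analysed is commonly left to an analysis plan.

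**Conclusion.** The point holds. As written, at least ten adherence comparisons at 0.05 answer the primary objective, with none designated as deciding and no control of the overall error. Under assumed correlations, the chance of at least one false-positive result is roughly 25–30% in the structured simulations, and 13–35% over common correlations of 0.9 to 0.3. About half of that is in favour of evriMED, against 5% and 2.5% for a single test. These figures assume that each test holds its own level. A fixed multiple such as five times is tempting, and lies within the range, but it rests on a chosen correlation. What does not depend on any assumption is that the deciding endpoint is not named and that the sample size points in two directions.

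**What to change.** Before recruitment, which the Trial status section says has not started, name one measure in one form as the single primary endpoint. Test it once at two-sided 0.05 with a cluster-adjusted model. Make the other measure, the mean or remaining cut-offs, and treatment outcome secondary.

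The choice consistent with the existing calculation is the proportion of participants with at least 95% adherence by refill count. The mean adherence wording in Sample size calculation and randomization should then be changed to match. If the mean is preferred, that is also a valid endpoint, but the sample size must be restated for a difference in means with an SD and its source. Either choice removes the inflation.

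The cost is a change of wording in the protocol and the registry entry. The downside is that the other measure and forms can no longer carry the claim. With refill count as the basis, the article's own caution that this measure overstates adherence applies to the primary result and should be acknowledged.

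### The primary adherence comparisons list unclustered t, nonparametric and χ² tests beside cluster-adjusted mixed models without saying which decides; the unclustered t-test has about 10.8% type I error at the protocol's own ICC

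*Protocol article*

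**What the plan says.** Under Data management and analyses, Primary objective, the protocol article compares mean adherence between arms, and also the percentage of participants reaching each of four cut-offs (99%, 95%, 90% and 75%). For the means it states: "For continuous adherence levels, we will use *t*-tests or nonparametric tests depending on distribution of data". For the cut-offs it names χ² tests. The paragraph closes with: "To account for the cluster effect in the analysis, we will conduct mixed effects regression models".

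The general text of Data management and analyses sets one level for all of these: "Statistical tests will be performed at a two-sided significance level of 0.05".

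Sample size calculation and randomization assigns six clusters to each arm and allows for clustering in the numbers: "As we will use cluster randomization, we used a cluster correlation factor of 0.01". It arrives at 600 patients, 50 in each of 12 clusters, and 660 after an allowance for drop-out.

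**The concern.** Clusters were randomised, not patients. Patients in one cluster share clinics, staff and catchment, so their outcomes are correlated. A t-test, rank test or χ² test on about 600 individual records takes them as independent, which makes the standard error too small, the p-value too low and the confidence interval too narrow.

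The mixed model sentence supplies a valid analysis of the same outcomes, but it neither withdraws the simple tests nor calls them descriptive. Two sets of p-values therefore stand side by side at the same 0.05 level, and only one set respects the design. If they disagree, the article gives no rule for which one counts. This matters because the Discussion part of the Abstract makes scale-up within the national programmes depend, among other things, on a significant effect on adherence.

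**Working it through.** **Inputs, all from the protocol article**
- Two-sided level 0.05 (Data management and analyses).
- From Sample size calculation and randomization: 79% versus 90%; power 80%; 336 patients before the cluster allowance (168 per arm); cluster correlation 0.01; 12 clusters of 50; six clusters per arm.
- Assumption: the cluster correlation factor is the intracluster correlation (ICC).

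**1. Reproduce the plan's own figure.** The usual two-proportion formula with pooled variance under the null, for 0.79 versus 0.90, gives 168.7, so 169 per arm; with unpooled variance it gives 166. The stated 168 lies between the two. The starting figure is thus an individual-level calculation for two proportions, with clustering added afterwards.

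**2. Design effect.** DE = 1 + (m − 1) × ICC = 1 + 49 × 0.01 = 1.49. The true standard error is √1.49 = 1.22 times the one that an unclustered test uses.

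**3. Type I error of an unclustered test.** 2 × [1 − Φ(1.96 / √1.49)] = 2 × [1 − Φ(1.606)] = 10.8%. With 55 enrolled per cluster, DE = 1.54 and the error is 11.4%.

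**4. Simulation under the null** (20,000 trials, six plus six clusters of 50, ICC 0.01, normal outcome):

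| Analysis | Rejects at nominal 5% |
|---|---|
| Ordinary t-test on patients | 10.7% |
| χ², 79% adherent, 0.01 on an underlying continuous scale | 7.7% |
| Mixed model, large-sample reference | 6.2% |
| t-test on cluster means, 10 df | 4.8% |

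A separate simulation with the 0.01 on the binary scale gave 11.0% for χ², in line with step 3. The range for χ² is therefore about 8 to 11%.

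**5. Sensitivity of step 3 to the ICC (m = 50).** The values other than 0.01 are assumptions and do not come from the article.

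| ICC | Type I error |
|---|---|
| 0.001 | 5.6% |
| 0.005 | 7.9% |
| 0.01 | 10.8% |
| 0.02 | 16.4% |
| 0.05 | 29.1% |

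**6. Power when inference rests on 12 clusters.** The summed binomial variance is 0.79 × 0.21 + 0.90 × 0.10 = 0.2559. SE = √(0.2559 × 1.49 / 300) = 0.0357. The non-centrality is 0.11 / 0.0357 ≈ 3.09. Against a t distribution with 10 df (critical value 2.228) the power is 79.4%; simulation gave 79.9%.

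**7. Interval width.** √1.49 × 2.228 / 1.96 = 1.39. A valid 95% interval with 10 df is about 1.39 times as wide as the unclustered one.

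**The case against.** The strongest reply is that the plan does account for clustering. The last sentence of the same paragraph names the problem and gives the remedy, for the same comparisons, and the sample size was enlarged for it. On a natural reading the simple tests are first-look comparisons and the mixed model carries the inference. This stands in part. A reader might infer that the trial as planned runs at 11% type I error; the article does not support that, because the mixed model holds about 5 to 6%. Nor does it support saying that the authors intend to report whichever result suits. What it shows is an unstated hierarchy.

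A second reply is that a condensed article may leave details to a statistical analysis plan. That is fair for the degrees-of-freedom method, the rule for choosing between a t-test and a rank test, and reporting of the observed ICC. Their absence is not held against the article. In particular, a reader might suppose that the mixed model will be read against a normal distribution. The article states no reference distribution, so this cannot be charged to it. The reply does not cover the unclustered tests, which are a stated choice and not an omission.

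A third tempting inference is that the figure of 600 proves that a cluster-based analysis was assumed, through a formula that adds one cluster per arm. The article names no formula. Plain inflation also reaches 600: 168 × 1.49 = 250.3 per arm, divided by 50 gives 5.007 clusters, rounded up to six per arm. The figure cannot settle which analysis was meant.

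**Conclusion.** The point holds in a limited form. The article names individual-level tests for the primary comparisons of a trial with 12 randomised clusters, sets them beside a valid mixed model, and makes neither decisive. If the unclustered t-test were taken as the answer, its type I error would be about 10.8% instead of 5%; for χ² it would be about 8 to 11%. The mixed model does not share this inflation.

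The sizes rest on the 0.01 being an ICC, on equal clusters of 50 and, for the upper χ² figure, on the 0.01 applying to the binary outcome. A smaller true ICC would shrink the excess and a larger one would increase it. The power figure treats 79% and 90% as proportions, as the stated 168 per arm suggests, although the article calls them mean adherence.

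**What to change.** In the Primary objective paragraph, remove the t, nonparametric and χ² tests as inferential analyses, or keep them only as labelled description without a claim of significance. State that the already planned mixed effects model, with a random cluster effect, is the sole basis for inference on adherence. Because there are only 12 clusters, specify small-sample degrees of freedom (Satterthwaite-type, for example). A t-test on the 12 cluster summaries with 10 df is a simple alternative. Whichever is chosen should be fixed before outcome data are seen; the article's Trial status section says that recruitment had not started.

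The cost is wording only. Intervals will be wider than unclustered ones, by the factor of about 1.39 shown above, but that is the width the design requires. Power for 79% versus 90% at ICC 0.01 is about 79%, close to the planned 80%, with no change in the number of patients or clusters.

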#### Secondary objectives

To assess accuracy, we will do unannounced pill counts and isoniazid urine tests, whereby we can measure whether pills really have been taken. The results from both tests will be compared to the data from the evriMED devices.

To assess the experience, feasibility, and acceptability of users, we will use qualitative data from interviews and focus group discussions. We will use thematic content analysis, in which recurrent themes are coded and classified in categories.

To assess technical feasibility of using evriMED in Tanzania, we will analyze data on network connection, sent and received messages, battery life of the devices, and other technical issues such as breakdowns of the boxes.

## Discussion

Adherence to treatment is a challenge for many TB patients. Many factors play a role. As such, interventions are needed that can tackle the variety of factors. EvriMED is a device for real time medication monitoring and will therefore be able to remind TB patients to take medication in case they forget. Other factors can be tackled through the suggested tailored feedback based on adherence reports from the evriMED device. The reports will be used as an entry point for discussing poor adherence and causative factors during consultation with health care providers. Therefore, we believe that evriMED might improve adherence to treatment and consequently improve TB treatment outcomes. One factor that we think might play a big role in implementing evriMED is perception of stigmatization as a consequence of using the device. Therefore, we will investigate stigmatization as a separate factor. If evriMED proves to be effective, it could be implemented on a wider scale and as such contribute to WHO’s END TB Strategy.

Stigmatization might limit the acceptability of evriMED. Several studies have shown that levels of stigmatization among TB patients are high [53–55]. We believe that the appearance of the evriMED box might contribute to higher levels of stigmatization. The box is white, is the size of a lunchbox, and also contains lights and sounds for alarming the patient to take medication. Furthermore, patients will receive reminder SMS messages. Other people seeing the box or the SMS may lead to unwanted disclosure of the condition to others. Additionally, TB patients might experience the fear of unwanted disclosure and consequent stigmatization. Our experience among PLHIV is that this fear is present based on previous pilot studies where we used SMS and RTMM [43]. Some participants of those studies mentioned actual situations of unwanted disclosure of their HIV status and the fear of stigmatization. To our knowledge, previous studies on using evriMED among TB patients in Sub-Saharan Africa have not been performed while WHO and other studies highly advocate for using RTMM and specifically evriMED. As we will measure stigmatization as a separate factor in our trial, we will be able to show whether stigmatization is a main challenge in implementing evriMED in our setting (Additional file 1).

